#### 2.6.3 Randomization and stratification.

We will use computer-based randomization without stratification using randomized blocks of small size and permutation of treatments within each block. Investigators, patients, and research staff will be blinded to the randomization list. Due to a secondary sample size calculation, the final randomization will be executed after the final sample size calculation.

### 2.7 Ethical concerns/ risk assessment

We plan a prospective pharmacological randomized cross-over single-center study to find out the effectiveness of dapagliflozin in high-risk patients with recurrent kidney stones. The current preventive therapies previously discussed vary widely and have low to zero success rates in many cases. [21,62,63]. The prospective collection and evaluation of blood and urine samples will determine the efficacy of dapagliflozin for this special group of patients. The performance of our study will be according to the principles of the Declaration of Helsinki 2008. The study has received approval from the Institutional Review Board of the Medical University of Vienna (1205/2022).

The planned study procedures in the current prospective observational project are all embedded in the standard of care procedures. At the study visits samples of blood and urine specimens (approx. 60 ml and 9 ml) will be collected to show if dapagliflozin therapy will produce results in this specific group of patients; that do not pose a potential harm to the study participants. However, we assume that no participant will be subjected to any potential harm related to their participation in the study. No interventional procedures will be performed if not clinically indicated. Due to the assumption that dapagliflozin will reduce the oxalate output, there is a probability that participants will experience a significant benefit from the study project. The results from this trial however have the potential of adding significant insight into the efficacy of dapagliflozin therapy in patients with a high risk of recurrent urolithiasis. These results potentially could be highly valuable for future patients in improving their quality of life, kidney function, and kidney stone-related mortality. This study was initially submitted to the EudraCT database under the identifier 2022-000994-13. However, per the regulatory transition requirements, the study has been submitted to the Clinical Trials Information System (CTIS) under the identifier 2024-519371-25-00. This ensures compliance with the latest clinical trial regulation (Regulation (EU) No 536/2014), which mandates the migration of EudraCT studies to CTIS for harmonized trial management and transparency. Both identifiers are provided for reference and traceability.

#### 2.7.1 Sex- and gender-specific aspects.

The prevalence of urolithiasis in Western countries is higher in men than in women. In the majority of cases, this is most likely related to previously mentioned lifestyle factors and underlying diseases. In all genders, an increasing prevalence has been detected in recent years.

In the application of Dapagliflozin, no significant sex- or gender-specific aspects related to side effects, response, outcome or any other issue have been described. Therefore, an age and sex-balanced patient population will be recruited for our study to produce data that most accurately will assess the relevant variables as determined by previous studies.

Females of childbirth potential are allowed to participate in this clinical trial if they declare to not try to actively become pregnant while participating in this study. There will be no obligatory contraception for these females. Pregnancy tests immediately before study inclusion and at least monthly during the study will be performed.

#### 2.7.2 Study discontinuation and management of serious adverse events (SAEs).

The study will be discontinued for any participant in the event of a serious adverse event (SAE), significant protocol deviations, or if continuation poses a risk to the participant’s health. Study discontinuation may also occur at the request of the participant or their treating physician. Criteria for discontinuing a participant’s involvement in the study include:

Occurrence of any SAE related to dapagliflozin or placebo that is life-threatening, results in hospitalization, or causes significant disability (diabetic ketoacidosis, severe urinary and genital infections, hypotension, acute kidney injury, fractures, and hypoglycemia).Persistent non-compliance with the study protocol, such as failure to attend required study visits or adhere to the treatment regimen.Development of any new medical condition or complication that contraindicates continued participation, such as a significant decline in renal function (eGFR <15 ml/min/1.73 m²) or other serious medical conditions requiring immediate treatment outside the scope of the study.At the participant’s request, for any reason, or if the participant becomes pregnant during the study period.

In the event of an SAE, immediate steps will be taken to ensure the participant’s safety, including withdrawal from the study treatment if necessary. All SAEs will be reported to the Institutional Review Board (IRB) within 24 hours of awareness, followed by a detailed report within seven days. If necessary, the IRB can recommend study suspension or termination depending on the frequency and severity of the events.

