#### 2.5.3 Primary endpoint of the main trial.

As the primary endpoint, we chose *the reduction of the urine oxalate excretion after 8 weeks of dapagliflozin therapy* compared to the baseline value that was collected in the washout phase before the treatment period.

As a secondary objective, we chose to compare the oxalate and calcium-sparing effects such as the kidney function, the frequency of urolithiasis events within the study period, and the tolerance to each treatment. The rationale behind this is a combination of two findings: 1) the reduced urolithiasis event rate under SGLT-2 inhibitor therapy in former trials [68, 69] and 2) the reduced oxalate excretion in a rat model about the effect of SGLT-2 inhibitors on urolithiasis [69]. Further, AstraZeneca holds a patent for the use of SGLT-2 inhibitors to prevent and treat kidney stones [81].

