## 3. Statistics

### 3.1 Statistical analysis

We plan to perform statistical analysis conforming to the standard methodology. Categorized data will be presented as absolute count and relative frequencies. Continuous data will be reported as mean and standard deviation in case of normal distribution and as median and inter-quartile range (IQR) in case of a non-normal distribution. Two-sided tests are considered to be significant with a p-value <0.05.

Analyses of continuous variables will be performed using parametric and non-parametric tests (paired t-test/ Mann-Whitney-U-test). The primary endpoint is confirmatory and is the reduction of oxalate in the Verum vs. Placebophase, i.e., Dapaglifozine vs. placebo which will be compared with a two sided-t-test. Intergroup comparisons (Dapaglifozine vs placebo) will be performed by an ANOVA for a crossover design on the group of patients who went through all trial phases and corrected with Bonferroni post-hoc Tests for multiple testing. Frequencies of urolithiasis will be tested with the x²-test, a in comparison of both treatments by the McNemar-Test. Correlations between variables will be performed using Pearson or Spearman coefficients.

Findings will be corrected for multiple testing using the Tukey method if the statistical analysis is performed with a one-way ANOVA or with the Shaffer correction if the statistical analysis is performed with a Kruskal-Wallis test. All other statistical tests will be corrected using the Bonferroni-Holm method.

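### Section 2.7.2 is inconsistent on when an SAE ends participation; under its widest reading, patients are also lost from the completers-only crossover ANOVA

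*Protocol article*

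**What the plan says.** Section 2.7.2 addresses an SAE in three places.

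- **Opening sentence:** "The study will be discontinued for any participant in the event of a serious adverse event (SAE), significant protocol deviations". It is mandatory and sets no condition on relatedness or severity.
- **Criteria list**, introduced by "Criteria for discontinuing a participant’s involvement in the study include": the SAE item reads "Occurrence of any SAE related to dapagliflozin or placebo that is life-threatening, results in hospitalization, or causes significant disability". A later item covers any new condition or complication that rules out continuing, including other serious conditions that need immediate treatment outside the study. That item has no relatedness condition.
- **Closing paragraph:** after an SAE, immediate safety steps are taken, "including withdrawal from the study treatment if necessary". This concerns treatment and is left to judgement.

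On the analysis side, section 3.1 plans an "ANOVA for a crossover design on the group of patients who went through all trial phases". Stone frequency is to be tested by chi-square and, "in comparison of both treatments by the McNemar-Test". Section 2.5.3 lists among the secondary objectives "the frequency of urolithiasis events within the study period, and the tolerance to each treatment". Section 3.2 sends patients with colic or a stone episode to an extra unplanned visit and does not mention discontinuation.

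**The concern.** Staff handling an SAE that is not attributed to study drug get different answers depending on which sentence they follow. The opening sentence ends participation. The SAE item in the list does not apply. The closing paragraph leaves treatment to judgement and is silent on participation.

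The choice also determines who is analysed. Participants are selected for high stone risk, so an SAE may itself be a stone event, which is a study outcome. If such an event removes the participant, the completers restriction removes that participant's oxalate data from the crossover ANOVA, and the paired stone comparison loses the pair. Participants who leave because of adverse effects of one treatment would be lost in the same way. Loss that depends on outcome or treatment can bias what remains.

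**Working it through.** **1. One event under each statement.** Take a participant admitted to hospital with a stone episode that the investigator judges unrelated to study drug. The article does not define an SAE. That this event counts as one is inferred from the list's mention of hospitalisation.

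| Statement in 2.7.2 | Consequence |
|---|---|
| Opening sentence | Participation ends |
| List, SAE item | Does not apply (not related) |
| List, item on other serious conditions | May apply, on judgement |
| Closing paragraph | Study treatment may or may not be withdrawn; nothing on participation |

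The list is introduced as non-exhaustive, so its SAE item could be read as an example. Its relatedness and severity conditions would then have no function, because the opening sentence already covers every SAE. The inconsistency therefore remains under either reading.

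**2. Consequence for the analyses.** A participant removed in treatment phase I or wash-out II never enters the second treatment phase.
- Crossover ANOVA: excluded by the stated restriction.
- McNemar: no complete pair. The test uses only discordant pairs, and an event in the first period followed by removal is potentially one of these.
- Chi-square on stone frequency: no completers restriction is stated, so the event can still be counted.
- Primary two-sided t-test: no analysis set is stated. A within-patient comparison would also need both periods, but the article does not write the restriction there.

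**3. Scale.** The plan gives no figure to reproduce. Inputs:
- Duration: weeks 7–40, that is 6 + 8 + 6 + 8 + 6 = 34 weeks, or 34/52 = 0.654 years.
- Recurrence figures: sections 1.1, 1.3.1 and 1.4.4.
- Share of stone events hospitalised: not given; assumed 25–50%.

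Formulas, with a constant hazard: rate = −ln(1 − p)/years; risk over 34 weeks = 1 − exp(−rate × 34/52); removed = risk × 0.25 to risk × 0.50.

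| Source figure | Rate per year | Risk, 34 weeks | Removed |
|---|---|---|---|
| Registry, 36 per 1,000 person-years | 0.036 | 2.3% | 0.6–1.2% |
| Registry, 53 per 1,000 person-years | 0.053 | 3.4% | 0.9–1.7% |
| 60% at 10 years | 0.092 | 5.8% | 1.5–2.9% |
| 40% at 5 years | 0.102 | 6.5% | 1.6–3.2% |
| 43% at 3 years (recurrent formers) | 0.187 | 11.5% | 2.9–5.8% |
| 80% at 3 years (recurrent formers) | 0.536 | 29.6% | 7.4–14.8% |

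Example, 43% at 3 years: −ln(0.57)/3 = 0.187; 1 − exp(−0.187 × 0.654) = 0.115; 0.115 × 0.25 = 0.029 and 0.115 × 0.50 = 0.058.

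The 75% at 20 years in section 1.3.1 falls inside the lower group: rate 0.069, risk 4.4%, removed 1.1–2.2%.

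Section 2.3.2 adds 20% to the calculated sample size for dropouts, which is 0.20/1.20 = 16.7% of those enrolled. The lower group (0.6–3.2%) uses little of that. The top of the upper group (14.8%) uses most of it.

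**The case against.** The strongest case on the other side is that this is one loose sentence and not a contradiction with consequences. Several parts of that case stand.

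- A reader might infer three mutually exclusive rules. The text does not support this. The closing paragraph is about study treatment and can stand beside a rule on participation, and the item on other serious conditions makes the list wider than its SAE item alone. The clear conflict is between the opening sentence and the SAE item. The closing paragraph adds ambiguity because stopping drug and leaving the study are not separated.
- A reader might infer that endangered patients could be kept on drug. They could not: section 2.7.2 also allows discontinuation whenever continuing poses a risk, or at the request of the participant or treating physician. The uncertainty lies in removing too many.
- A reader might infer that the primary analysis is restricted to completers. Section 3.1 attaches the restriction to the crossover ANOVA only.
- A reader might take bias as established. No direction or size for the oxalate contrast follows from the document.
- A reader might take 3–15% as the expected loss. That range uses only the highest recurrence figures, which apply to recurrent formers, while section 2.4.3 also admits single-stone formers with risk factors. The article does not say that those recurrences were symptomatic. The 34 weeks also include wash-out III, where events after the week-35 sample follow the last treatment-response measurement.

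It can also be said that separating end of drug from end of follow-up is often left to a full protocol. That would hold if the article were silent. Here it states a mandatory exit rule and a completers-only analysis, and the two interact as written.

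**Conclusion.** The point holds in a limited form. Section 2.7.2 is internally inconsistent on when an SAE ends participation; this rests on the text alone and needs no assumption. Under its widest reading, combined with the completers restriction in section 3.1, participants with unrelated SAEs are lost from the crossover ANOVA and from the McNemar comparison. Some of that loss can be related to outcome, so it can bias those two comparisons. The effect on the primary t-test cannot be stated, because its analysis set is not given.

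For hospitalised stone episodes alone, the loss would be about 0.6–3.2% of participants at the registry, 5-year and 10-year rates, and about 3–15% at the three-year rates for recurrent formers. This assumes a constant hazard, 25–50% of events hospitalised, every such event counted as an SAE, and the opening sentence applied literally. At the lower rates the numbers are small, but the loss would still depend on a study outcome.

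**What to change.** 1. Reconcile the statements in section 2.7.2 into one rule on when an SAE ends participation. Which rule applies is for the investigators to decide.
2. In the same section, distinguish the end of study drug from the end of follow-up, so that stopping one does not by default stop the other. Where follow-up continues, both periods remain observable for the stone comparison.
3. In section 3.1, fit the crossover comparison to all available period data, for example by a mixed model with treatment, period and sequence, instead of completers only. Keep the completers analysis as a sensitivity analysis. The mixed model relies on missingness that depends only on observed data; this is weaker than what the completers analysis needs, but it is still an assumption to state.

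The cost is a short rewording of section 2.7.2 and a line or two in section 3.1. The analysis change needs no additional participants.

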#### 2.7.3 . Informed consent form (ICF).

Before joining this study, all participants will be asked to review and sign an informed consent form. This process is designed to ensure that each participant:

Understands Why the Study is Being Conducted: Participants will receive clear information about the study’s goals, what we hope to learn, and what participation will involve.Knows Participation is Voluntary: Participation in this study is entirely voluntary. Patients will be reassured that they are free to withdraw at any time without any impact on the quality of their usual medical care.Is Informed About Potential Risks and Benefits: We will explain any potential risks, benefits, or discomforts associated with the study in plain language. Participants will be fully informed about what to expect, including any possible side effects related to treatments being studied.Is Assured of Confidentiality: Participants will be informed of how their information will be kept secure and used strictly for research purposes. Personally identifiable information will remain confidential and protected throughout the study.Has the Chance to Ask Questions: We encourage participants to ask any questions they may have about the study, the procedures, or what their involvement means. Our goal is to ensure they feel comfortable and informed before signing.

#### 2.7.4. Dietary compliance monitoring.

All participants will receive clear, written dietary instructions and regular reminders during study visits to promote adherence. Compliance will be monitored through dietary adherence questionnaires completed at each study visit throughout the study. Although perfect adherence cannot be guaranteed, any non-compliance will be documented and addressed with participants as needed. Significant deviations from the dietary instructions will be considered during the analysis phase as potential confounding factors to ensure a robust interpretation of the results.

## 3. Statistics

### 3.1 Statistical analysis

We plan to perform statistical analysis conforming to the standard methodology. Categorized data will be presented as absolute count and relative frequencies. Continuous data will be reported as mean and standard deviation in case of normal distribution and as median and inter-quartile range (IQR) in case of a non-normal distribution. Two-sided tests are considered to be significant with a p-value <0.05.

Analyses of continuous variables will be performed using parametric and non-parametric tests (paired t-test/ Mann-Whitney-U-test). The primary endpoint is confirmatory and is the reduction of oxalate in the Verum vs. Placebophase, i.e., Dapaglifozine vs. placebo which will be compared with a two sided-t-test. Intergroup comparisons (Dapaglifozine vs placebo) will be performed by an ANOVA for a crossover design on the group of patients who went through all trial phases and corrected with Bonferroni post-hoc Tests for multiple testing. Frequencies of urolithiasis will be tested with the x²-test, a in comparison of both treatments by the McNemar-Test. Correlations between variables will be performed using Pearson or Spearman coefficients.

Findings will be corrected for multiple testing using the Tukey method if the statistical analysis is performed with a one-way ANOVA or with the Shaffer correction if the statistical analysis is performed with a Kruskal-Wallis test. All other statistical tests will be corrected using the Bonferroni-Holm method.

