### 1.5 Need for new treatment options

The large individual and economic burden upon the health care system demands fundamental changes in the treatment and prevention of urolithiasis. The recommended lifestyle changes including increasing fluid intake, weight loss, reduction of sodium consumption, and increase of potassium-rich foods are difficult to adhere to and often only of short benefit. For instance, even under the conditions of an RCT where intensive coaching was applied to increase water intake, the treatment effect was mild with an increase of urinary volume of 0.6 L/day in the treatment group [77]. Similar findings have been observed in pragmatic RCTs aiming at weight reduction through structured coaching on behavioral changes [78].

The current drug treatment options are limited by tolerance, side effects, and low efficacy of therapy. Therapy with HCT has been shown to have no benefit compared with the placebo group in the frequency of events nor in the risk of reoccurrence independently of the dosage. Additional to the lack of efficacy in this specific indication it should be emphasized that long-term therapy with HCT increases the risk of melanoma and non-melanoma skin cancer in non-Asian countries, and regular screening for this skin cancer is necessary [79]. Due to this fact, HCT is no longer recommended by the guidelines of 2023 of the German Urology Association as prevention therapy for recurrent kidney stone patients. Alkaline citrate supplementation may provide beneficial effects in hypocitraturia, but its application is limited by reduced gastrointestinal tolerance, leading to treatment discontinuation in a large proportion of patients.

In summary, in the current situation, there exists no relevant and effective therapy options for the mass of patients with a high risk of reoccurrence based on a significantly increased risk of and/ or an increased number of urolithiasis events within the past years. Further research is needed to identify at least one option for this specific group of patients. If successful, decreasing the frequency of recurrent nephrolithiasis would increase the quality of life for these patients and reduce morbidity and healthcare-related costs.

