### 2.6 Study schedule

We plan to do blood- and 24-hour-urine screenings including oxalate and citrate as well as metabolomics tests out of blood and urine samples at crucial points of time of the study to get baseline and therapeutic data of the participants. The primary endpoint is confirmatory and is the reduction of oxalate in the *Verum* vs. Placebophase, i.e., Dapaglifozine vs. placebo which will be compared with a two sided-t-test.

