#### 2.6.2 Main trial phase.

The main trial will start with wash-out phase I. All patients will receive blood- and 24-hour-urine screenings in week 6 (respectively week 12 overall) to get baseline data. In preparation for the treatment phase I all participants will receive a daily oral placebo administration over the whole period and will be randomized in two groups.

In week 13 the treatment phase I will start and group 1 will receive oral therapy with 10mg of dapagliflozin while group 2 will get an oral placebo administration daily; the treatment response will be evaluated by blood- and urine test after 4 weeks of therapy (respectively week 16 overall) and in the beginning of in washout phase II (respectively week 21 overall). The same test as before will be performed after 6 weeks (respectively week 26 overall) to gain baseline data for treatment phase II. In preparation for the treatment phase II, all participants will receive a daily oral placebo administration. will receive a daily oral placebo administration.

In the end, we will perform treatment phase II with an oral administration of 10mg of dapagliflozin for group 2 and daily placebos for group 1. The treatment response will be evaluated by blood- and urine tests after 4 weeks of therapy (respectively week 30 overall). Finally, the same tests as before will be performed in wash-out phase III in weeks 1 and 6 (respectively weeks 35 and 40 overall). This way we will get data of the non-therapy periods and of the outcome that will be caused by the dapagliflozin therapy. For each patient, a comparison will be made between the excretion of the electrolytes and molecules of the primary and secondary endpoints under dapagliflozin therapy vs. oral placebo administration.

Throughout the whole study procedure, all participants will be advised to follow dietary instructions as recommended in the urolithiasis guidelines of 2023 [62]. The requested measures will include a balanced diet including a high ratio of vegetables and fibers, a low-fat diet, a calcium intake of about 1.0 to 1.2g per day, a reduced intake of salt up to a maximum of 4.0 to 5.0g per day and an intake of animal proteins of 0.8 to 1.0g per kg per day may reduce stone development risk. Furthermore, patients are strongly advised to not lose or gain weight tremendously throughout the trial process so that the date will be comparable over the whole trial period.

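### The confirmatory test of the two-period crossover is a t-test without a period term, although a crossover ANOVA is named for the same contrast

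*Protocol article*

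**What the plan says.** Section 3.1 of the protocol article states: "The primary endpoint is confirmatory and is the reduction of oxalate in the Verum vs. Placebophase". It names the test in the same sentence: "Dapaglifozine vs. placebo which will be compared with a two sided-t-test". Section 2.6 repeats it ("which will be compared with a two sided-t-test"). Neither place mentions period, and neither says whether the test is paired. Paired is the likelier reading, because the preceding sentence of 3.1 lists a paired t-test and the sample size in 2.3.1 rests on one.

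Section 3.1 then continues: "Intergroup comparisons (Dapaglifozine vs placebo) will be performed by an ANOVA for a crossover design". This analysis is restricted to patients who completed all phases. The bracketed contrast is the same dapagliflozin-versus-placebo comparison, but the word confirmatory is not attached to it.

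Section 2.5.3 defines the endpoint as the oxalate reduction after 8 weeks "compared to the baseline value that was collected in the washout phase before the treatment period". Section 2.6.2 supplies one baseline per period: week 12 for treatment phase I, and for the second period a repeat "after 6 weeks (respectively week 26 overall) to gain baseline data for treatment phase II". The urines that close the two treatment phases fall in weeks 21 and 35. The last sentence on the schedule in 2.6.2 speaks of comparing excretion under the two treatments and does not mention change from baseline.

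**The concern.** In a two-sequence, two-period crossover, half the patients take dapagliflozin first and half take placebo first. A difference between the periods that has nothing to do with the drug therefore enters the within-patient contrast with opposite signs in the two sequences. A model with a period term removes it; a paired t-test pooled over the sequences does not. If the sequences finish with equal numbers, the difference becomes noise. If they finish unequal, part of it is left in the estimated drug effect.

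The closing urines are 35 − 21 = 14 weeks apart. Section 1.5 says of lifestyle measures in general that they "are difficult to adhere to and often only of short benefit", and every patient in the main trial receives dietary advice. A change in behaviour over the trial is therefore possible. At stake are some power and the accuracy of the estimated reduction, in the one analysis that decides the trial.

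**Working it through.** **Inputs from the documents.** For the 25% row of Table 1: SDs 0.20 and 0.25, correlation 0.1 (2.3.1), 18 completers, 22 with dropout. Two equal groups (2.4.2) means 11:11 randomised if the total is 22.

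**Assumed, not in the documents.** The difference p between the periods (0, 0.10 or 0.20 of the mean) and the completers per sequence (9:9 or 11:7). The plan gives no SD for a change from baseline, so its own SD for the paired difference is used for the treatment contrast.

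**Reproducing the plan's figure.** SD of the paired difference = √(0.20² + 0.25² − 2 × 0.1 × 0.20 × 0.25) = √0.0925 = 0.304. A paired t-test at two-sided 0.05 with 90% power gives group sizes of 86, 42, 26, 18 and 14 for the five rows, exactly as in Table 1. The calculation below therefore uses 0.05. Sections 2.3.1 and 2.3.2 also state 0.025, so that level is shown too.

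**How period enters.** Let p be the period 1 level minus the period 2 level. The expected dapagliflozin-minus-placebo difference is effect + p in one sequence and effect − p in the other.

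**Balanced completion.** The +p and −p cancel in the mean, so there is no bias. They add about p² to the variance of the differences:
- p = 0.10: (0.0925 + 0.01)/0.0925 = 1.11
- p = 0.20: (0.0925 + 0.04)/0.0925 = 1.43

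Simulated results for 9:9 with a true effect of 0.25:

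| Period difference | Plain t-test, power at 0.05 | Period-adjusted, power at 0.05 | Plain t-test, type I error at 0.05 | Plain t-test, power at 0.025 | Period-adjusted, power at 0.025 |
|---|---|---|---|---|---|
| 0 | 91% | 90% | 5% | 84% | 83% |
| 0.10 | 88–89% | 90% | 4% | 80% | 83% |
| 0.20 | 82% | 91% | 2% | 69% | 83% |

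The period-adjusted test keeps a type I error of about 5% throughout.

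**Unequal completion.** The size of the bias is p × (difference in completers)/N. With four dropouts from 22, the worst split is 11:7:
- p = 0.10: 0.10 × 4/18 = 0.022
- p = 0.20: 0.20 × 4/18 = 0.044

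Its direction depends on the sign of p and on which sequence loses patients. At this split the plain test's type I error stays at about 4–5%. The period-adjusted estimate has no bias, and its power is about 89%.

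**How likely is 11:7?** If dropout is unrelated to sequence, the chance that all four dropouts come from one sequence is 2 × C(11,4)/C(22,4) = 660/7315, about 9%. Averaged over all splits the bias is then zero.

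**The case against.** The strongest objection is that the plan does not ignore period. The sentence after the t-test names a crossover ANOVA for the same contrast, and the exact terms of that model may properly be left to an analysis plan that is not shown. This stands as far as it goes: a reader might infer that the plan contains no period-adjusted analysis, and that would be wrong. But the article does fix which test is confirmatory, twice, and it is not that one. The wording could be stretched to cover a two-sample t-test of within-patient period differences, which does adjust for period. Nothing in the text says that this is meant.

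Second, each period has its own washout baseline. Drift already present at week 26 cancels when changes are compared. A reader might infer that any drift over the 14 weeks is counted as a drug effect; under the endpoint definition in 2.5.3 it is not. What remains is a difference between the periods in within-period change, or all drift if raw excretion is compared, as the wording of 2.6.2 allows.

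Third, a reader might infer more false-positive results. With balanced sequences the reverse holds: type I error falls to 4% or 2%. At 11:7 it stays near nominal.

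Fourth, the evidence for drift is indirect. Section 1.5 is general background and reports nothing on urinary oxalate. The trial gives constant dietary instructions, monitors adherence at each visit (2.7.4) and places a placebo wash-out before each treatment phase. This is a fair limit on the size of the problem, though 2.7.4 itself grants that perfect adherence cannot be guaranteed.

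Last, 18 completers is the exploratory-phase figure. The main-trial size is to be recalculated, and the abstract gives a range of 17 to 104.

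**Conclusion.** The point holds in a limited form. The article attaches the confirmatory label to a t-test without a period term and leaves the better-suited analysis, already named for the same contrast, without that status. It thus names two analyses for one question and gives the deciding role to the weaker one.

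The consequence is modest. With balanced completion the plain test loses about 2 points of power at an assumed 10% period difference and about 9 points at 20%. With the worst split of the planned dropouts, the estimate moves by 2.2 or 4.4 points, in either direction. These sizes rest on the assumed period differences, on the plan's SD and correlation, and on 18 completers. If changes from the period-specific baseline are analysed, 10% and 20% must be read as differences in within-period change, for which the documents offer no figure. With a small period difference and near-balance, the two analyses will agree closely.

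**What to change.** In 2.6 and 3.1, make the crossover ANOVA already named the single confirmatory analysis. Its outcome should be the oxalate change from the period's own washout baseline, with treatment and period as fixed effects and patient as a random effect. Remove the plain t-test as the confirmatory test. Align the comparison sentence in 2.6.2 with the baseline-referenced endpoint in 2.5.3, so that raw excretion is not taken as the outcome.

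The cost is wording and one degree of freedom. With no period effect, simulated power goes from 90.6% to 90.3% at 9:9 and from 91.0% to 89.1% at 11:7, so at most about 2 points are lost.
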